### 2.3.2 Potential Benefits

There are important benefits of the proposed Caripil treatment on the study population. A number of studies have demonstrated the effectiveness of Caripill in increasing the total as well as rate of platelet counts and hematocrit levels in dengue patients with mild to moderate. Give the high risk of hemorrhages and shock in severe dengue cases and its associated mortality, any potential benefit of improvement in thrombocytopenia will be highly beneficial.

1. OBJECTIVES
   1. Study Objectives

Thrombocytopenia is a well-known risk factor of fatality in severe dengue cases. A steady decline in platelet counts is characteristically associated with dengue illness severity. Thrombocytopenia coupled to severe vascular leakage and shock, usually around the time of defervescence can prove to be fatal. We hypothesize that administration of CPLE (Caripill) tab early in the course of dengue illness increase the platelet counts and reduce the likelihood of severe complications.

The clinical benefit of CPLE (Caripill) administration on the platelet counts in mild and moderate dengue have been shown before, this study will present an opportunity to specifically evaluate the effectiveness of CPLE (Caripill) administration in severe thrombocytopenic (≤ 30,000/µL) dengue cases. We will also investigate the effect of CPLE on the viremia (or NS1 antigenemia) as well as the infection induced immune response.

Primary Objectives:

1. To evaluate if CPLE (Caripill) administration (1100 mg three times a day for 5 days) in dengue patients with thrombocytopenia ≤30,000/µL is superior to placebo with respect to improvement in platelet counts and hematocrit values.
2. To evaluate if CPLE (Caripill) administration (1100mg three times a day for 5 days) in dengue patients with thrombocytopenia ≤30,000/µL is superior to placebo with respect in reducing the number of platelet transfusions needed in management.
3. To determine and compare the incidence of bleeding episodes during hospitalization between the treatment and placebo groups. Bleeding will be defined as mucosal bleeds such as subcutaneous bleeding, minor mucosal hemorrhages, sub-conjunctival hemorrhage, epistaxis, petechiae, or ecchymosis, positive tourniquet test.
4. To evaluate the final outcome of dengue illness (survival/mortality rates) between the treatment and placebo groups.

Secondary Objectives:

1. To correlate the changes in platelet counts to the clinical phase of dengue illness (febrile/critical (plasma leak)/ convalescent) between the treatment and placebo groups.
2. To compare and evaluate the viremia (or NS1 antigenemia) with peripheral platelet counts between the treatment and placebo groups.
3. To evaluate length of hospital (ICU & ward) stay in patients receiving CPLE (Caripill) for severe dengue.
4. To compare and evaluate the levels cytokines TNFα, IFNγ, IL4 and IL6, on day 0, and 3 of study period between the treatment and placebo groups.
   1. Study Outcome Measures
      1. Primary

The primary efficacy endpoints will be assessed by comparing the increase in the platelet counts and hematocrit levels during the hospital stay between the treatment and placebo groups. The peak platelet count and hematocrit will also be noted and compared between the treatment and the placebo group. Additionally, the frequency and type of blood product, more specifically platelet transfusions required to manage thrombocytopenia during the course of illness will be compared between the two study arms.

Safety and tolerability will also be evaluated by comparing the proportion of patients with any AE (adverse event), and with any SAEs, between the treatment arms. The incidence of bleeding episodes as assessed by clinical evaluation twice daily between the treatment and placebo groups will also be evaluated. Evidences of subcutaneous bleeding minor mucosal hemorrhages, sub-conjunctival hemorrhage, epistaxis, petechiae, or ecchymosis), positive tourniquet test, hypotension and internal organ bleeding, hematemesis, intracranial bleed and melena will be assessed.

- - 1. Secondary

Secondary outcomes that we plan to evaluate include parameters indicative of disease progression or worsening of illness. These will be compared between the two study arms.

1. To correlate the change in platelet counts and subsequent response with or without CPLE (Caripill) to the phase of dengue (febrile/critical (plasma leak)/ convalescent) We will study the correlation of the duration of moderate to severe thrombocytopenia with the phase of the dengue- febrile, critical-plasma leak, convalescence. Additionally we will compare both arms of the study to examine if the intervention in any of the three phases affected the duration/severity of thrombocytopenia.
2. The type of bleeding manifestation between the two arms of the study will be characterized. We will examine the evidence of (mucosal, GI, GU, vaginal, IC bleed etc.) bleeding with severity of thrombocytopenia and response to intervention by comparing both arms.
3. Date of admission and date of discharge or death will be noted in the CRFs and will be used to determine the length of hospital stay (ICU & Ward), in severe thrombocytopenic dengue patients receiving CPLE (Caripill) treatment compared to the placebo group.
4. Other additional exploratory outcomes, intended primarily to evaluate the infection induced inflammatory response will be performed. Viral antigenemia and host immune responses are important determinants of disease severity and clinical outcome. Therefore, changes in the kinetics and levels of cytokines in severe thrombocytopenic dengue patients receiving CPLE (Caripill) therapy will be compared to the placebo group.

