**Dengue and Thrombocytopenia**

Thrombocytopenia, marked by a platelet count less than 150,000/µl of blood, is one of the hallmark indicators of severity in dengue viral infections. Typically platelet counts decline steeply during the infection within the initial 4-6 days of onset of fever and revert back to normal levels in the consequent days as the fever subsides. During the phase of defervescence, plasma leakage due to increased vascular permeability could potentially exacerbate the condition, leading to life threatening dengue shock syndrome (DSS) in patients with hemorrhagic fever (DHF) ^6^. Previous studies have reported an association between depleted platelet levels and higher prevalence of clinical bleeding in patients with dengue viral infections^7^. Inadequate platelet levels that fail to suppress bleeding and initiate coagulation could also lead to the bleeding symptoms. One of the several mechanisms proposed to explain thrombocytopenia during the infection of DENV serotypes involves the inhibition of bone marrow progenitor cell proliferation and functions^8^. Decline of megakaryocyte progenitors in the bone marrow has been demonstrated during dengue viral infection in humanized mice, possibly indicating the suppression of platelet production leading to dengue induced thrombocytopenia^9^. Depletion of platelets during dengue viral infection can also be attributed to the activated immune response that destroys platelets by augmented apoptosis, lysis and antibodies^10^. The non-structural protein NS1 is expressed in infected cells, eliciting immune responses. DENV infections also lead to up-regulation of membrane bound Tissue Factor (TF) and activation of platelets. Coagulation and inflammatory pathways are initiated, leading to the release of pro-inflammatory cytokines like TNF-α and IL-6. Raised levels of TNF-α has been associated with hemorrhagic symptoms. Moreover, immune dysregulation can also lead to alterations in platelets functions. Plasma leakage from capillaries has also been associated to altered platelet functions^11^ Endothelial sequestration is another mechanism that leads to thrombocytopenia. Platelets increasingly attach to von-Willebrand factor (vWF) on vascular endothelial cells, resulting in small clogs in microcirculation and low levels of platelets in the peripheral blood^12^.

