1. STATISTICAL CONSIDERATIONS

**10.1 Sample size**

This is an exploratory study focusing primarily on efficacy of CPLE (Caripill) and based on earlier efficacy studies in mild and moderate dengue, a target sample size of 50 patients in 2 cohorts was chosen for enrolment over one year of dengue season based on clinical judgement and feasibility considerations.

Specifically, this study will have 80% power to detect an increase in platelet count and hematocrit levels by 20% due to CPLE (Caripill) therapy.

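### The primary efficacy endpoint counts an increase in hematocrit as benefit, but plasma leakage also raises hematocrit, so a between-arm rise is ambiguous and could score harm as success

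*Protocol*

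**What the plan says.** Primary Objective 1 (Objectives, Study Objectives) tests whether CPLE "is superior to placebo with respect to improvement in platelet counts and hematocrit values". It does not say which way hematocrit has to move.

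Three other places give the direction:

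- Study Outcome Measures, Primary: "The primary efficacy endpoints will be assessed by comparing the increase in the platelet counts and hematocrit levels during the hospital stay".
- Section 10.1, Sample size: "this study will have 80% power to detect an increase in platelet count and hematocrit levels by 20% due to CPLE (Caripill) therapy".
- Section 2.3.2, Potential Benefits, cites earlier studies as showing Caripill effective in "increasing the total as well as rate of platelet counts and hematocrit levels in dengue patients".

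The primary outcome adds that "The peak platelet count and hematocrit will also be noted and compared between the treatment and the placebo group", without saying whether a higher peak hematocrit is better. The Protocol Summary is neutral: it speaks only of the impact of CPLE on platelet count and hematocrit.

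On leakage, the background on dengue and thrombocytopenia says that "plasma leakage due to increased vascular permeability could potentially exacerbate the condition, leading to life threatening dengue shock syndrome". The Study Objectives text adds that thrombocytopenia combined with severe vascular leakage and shock can be fatal. The secondary objectives and outcomes label the critical phase of the illness as the plasma-leak phase.

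**The concern.** A primary superiority endpoint needs a direction that means benefit. For platelet count in patients at or below 30,000/µL, up is plausibly good. For hematocrit, up can mean recovery or loss of plasma into the tissues, which is the process the protocol itself presents as dangerous. Patients are treated and measured through the period in which that leak may occur.

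Hematocrit is named beside platelet count in the primary objective, the primary endpoint and the power statement. A significant hematocrit increase on CPLE could therefore be reported as primary efficacy although part or all of it came from leakage. Equally, a treatment that reduced leakage could look worse on this measure.

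**Working it through.** **1. The plan's own figure.** Section 10.1 states 80% power for a 20% increase. The schematic gives 50 per arm. SD, alpha and sidedness are not stated there, so the 80% can be neither confirmed nor refuted. Assuming alpha 0.05 and a comparison of two means, the relative SD (SD divided by the control mean) that yields 80% is 0.20 / [(z for alpha + z for power) × √(2/50)]:

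- two-sided: 0.20 / [(1.960 + 0.842) × 0.2] = 0.357
- one-sided: 0.20 / [(1.645 + 0.842) × 0.2] = 0.402

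Two-sided power for a 20% difference is above 99% at relative SDs of 0.10–0.20, 92% at 0.30, 52% at 0.50 and 17% at 1.0. A single 80% figure fits both platelets and hematocrit only if their relative SDs are equal. This is context; the point below does not depend on it.

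**2. Which direction counts.** Read together, the outcome section (increase), section 10.1 (increase by 20%) and section 2.3.2 (increase listed as effectiveness) make *improvement* in Primary Objective 1 mean upward.

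**3. What leakage does to hematocrit.** Let H = R / (R + P), where R is red-cell volume and P is plasma volume. With R fixed, a fall in P raises H. This follows from the definition alone.

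**4. Size of leak that alone gives a 20% relative rise (illustration).** Assume fixed R and a within-patient change.

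- Blood volume falls to 1/1.2 = 0.833 of its starting value, a loss of 1 − 0.833 = 16.7%, all of it plasma.
- As a share of plasma this is 0.1667 / (1 − H). Baseline H is not given in the protocol, so a range is assumed:

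| Assumed baseline H | H after a 20% rise | Plasma lost |
|---|---|---|
| 0.30 | 0.36 | 0.1667/0.70 = 23.8% |
| 0.35 | 0.42 | 0.1667/0.65 = 25.6% |
| 0.40 | 0.48 | 0.1667/0.60 = 27.8% |
| 0.45 | 0.54 | 0.1667/0.55 = 30.3% |

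**5. Smaller leaks act the same way.** For a plasma loss of fraction L, the new H is H / [H + (1 − H)(1 − L)]. For assumed baselines of 0.35–0.45:

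- L = 10%: relative rise 5.8–7.0%
- L = 20%: 12.4–14.9%
- L = 30%: 19.8–24.2%

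**6. Does anything in the protocol separate the causes?** No text restricts the hematocrit endpoint to patients without leakage, sets a target range, or distinguishes recovery from hemoconcentration. The analysis by illness phase concerns platelets. Section 10.3 adjusts laboratory markers among the secondary endpoints for pre-dose value and day of illness, and adds illness phase only for cytokines and NS1. Such adjustment would in any case not say whether a rise is good or bad.

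**The case against.** A reader might infer that the endpoint runs backwards, so that an arm with more leakage would win. The protocol does not support that. Its background on CPLE gives reasons for a rise without leakage: murine work reporting a red-cell increase, and in vitro work suggesting protection against hemolysis. In patients at risk of bleeding, less bleeding would also keep hematocrit higher. Fluids and bleeding pull it down. The supportable word is *could*.

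A reader might also infer that the objective itself, or the peak comparison, scores a higher value as better. The objective says only improvement, and the peak is merely to be compared. The direction comes from the outcome, sample-size and potential-benefits texts.

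The 16.7% figure has limits. Section 10.1 does not say whether 20% is a change from baseline or a difference between arms. If it is between arms, leakage would have to differ by that much on average because of CPLE, a far less ordinary event. Smaller differential leaks would still push the comparison the same way.

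Finally, serious leakage would not go unseen. Mortality, adverse events, hypotension, bleeding and ICU or ward stay are compared as well, the platelet comparison is unaffected, and section 10.1 calls the study exploratory. All of this stands and tempers the consequence. None of it gives a hematocrit increase one clear meaning, and an SAP should not be left to reverse a direction that the protocol has fixed.

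**Conclusion.** The point holds in a limited form. The protocol fixes an upward direction for hematocrit as primary efficacy, while naming as dangerous a process that also raises hematocrit. A between-arm rise is ambiguous: it could reflect benefit or leakage, and the plan offers no way to tell which.

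The 16.7% loss of blood volume (about 24–30% of plasma volume) for a 20% rise is an illustration. It rests on fixed red-cell mass, a within-patient change, no offsetting fluids or bleeding, and assumed baseline hematocrits of 0.30–0.45. It shows that leakage alone can produce a rise of the targeted size, not that it would do so here. No change to the sample size follows from this point.

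**What to change.** - Remove hematocrit from Primary Objective 1, from the primary efficacy endpoint (including the peak comparison listed there) and from the power sentence in section 10.1. Make the objectives in the Protocol Summary consistent.
- Report hematocrit by arm as a two-sided safety and disease-progression measure over the in-hospital period already specified, for example the maximum percent rise and the maximum percent fall from baseline. Flag patients who received red-cell transfusions.
- Leave platelet count and the other primary items (transfusions, bleeding, mortality) as they are.

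The cost is a wording change and one table. Hematocrit is already measured at least daily, and the type of blood product transfused is already to be compared. The downside is one fewer primary efficacy claim.

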**Randomization**

**Treatment Group (N=50)**

**Control Group (N=50)**

**Day 0**

Clinical examination and detailed biochemical, hematological and virological laboratory investigations will be performed at baseline. Peripheral blood (5ml) will be collected; CRF will be completed for each enrolled subject. Administer CPLE (Caripill) or placebo *t.i.d* for 5 days.

Repeat study intervention (*if applicable*).

Follow-up assessments of study endpoints and safety. Appropriate recommended “standard of care” treatment modalities will be employed for each study subject. Routine hematological and biochemical laboratory assays will be done. Administer CPLE (Caripill) or placebo *t.i.d* for 4 more days.

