**5.1 Subject Inclusion Criteria**

In order to be eligible to participate in this study, an individual must meet all of the following criteria:

1. Provide signed and dated informed consent form
2. Willing to comply with all study procedures and be available for the duration of the study
3. Male or female, aged ≥ 18 yrs of age. Clinically diagnosed of dengue and a peripheral platelet count of ≤30,000/µL.
4. A laboratory positive diagnosis of dengue confirmed by a positive NS1 or IgM or IgG ELISA test and/or detection of viral RNA by real time PCR assay.

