**5.2** **Subject Exclusion Criteria**

Patients with one or more of the following criteria at enrolment will be excluded from the study:

- 1. Pregnancy and lactation.
  2. Patients who has been given steroids for thrombocytopenia and also those who have been transfused platelets before starting the drug
  3. Taking indigenous medicines.
  4. Alanine aminotransferase (ALT) >150 U/L

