1. STUDY SCHEDULE

Screening

All adult patients admitted to Gen Medicine with a history of fever (<72 hr) will be clinically and laboratory evaluated for dengue illness. Subsequent to obtaining and documenting an informed consent form, the study subject will be further screened for detailed laboratory diagnosis for dengue and reviewed clinically for satisfying all study inclusion and exclusion criteria. Details in Schedule of Events

Detailed history and clinical examination will be performed and data recorded in the study CRF. Baseline hematological and biochemical, virological parameters (as part of standard of care) will be sought and recorded in the CRF. Study subject will be administered the study medications on day 1 after confirmed diagnosis as per schedule. Clinical evaluations, laboratory investigations including viral load will be performed during hospital stay.

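### The primary bleeding outcome is counted over the hospital stay, with no start at first dose and no new-onset condition, so pre-dose signs can count and dilute the comparison

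*Protocol*

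**What the plan says.** Bleeding is the third primary objective in the protocol's Study Objectives: "To determine and compare the incidence of bleeding episodes during hospitalization between the treatment and placebo groups". The definition lists mucosal and skin signs, ending with "sub-conjunctival hemorrhage, epistaxis, petechiae, or ecchymosis, positive tourniquet test". The primary part of Study Outcome Measures repeats the outcome in its safety and tolerability paragraph: "The incidence of bleeding episodes as assessed by clinical evaluation twice daily between the treatment and placebo groups will also be evaluated". Neither place gives a start time tied to randomisation or first dose, or asks that a sign be new or worse.

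Eligibility (section 5.1) requires "Clinically diagnosed of dengue and a peripheral platelet count of ≤30,000/µL". The background on dengue and thrombocytopenia states: "Previous studies have reported an association between depleted platelet levels and higher prevalence of clinical bleeding in patients with dengue viral infections". The exclusion list (section 5.2) has no item for patients who already show bleeding signs. The nearest item is "Patients who has been given steroids for thrombocytopenia and also those who have been transfused platelets before starting the drug".

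Treatment starts some time after admission. Under Study Schedule, admitted patients are evaluated, consented and laboratory-confirmed, and then "Study subject will be administered the study medications on day 1 after confirmed diagnosis as per schedule". The schematic plans a pre-treatment assessment: "Clinical examination and detailed biochemical, hematological and virological laboratory investigations will be performed at baseline".

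Section 10.2 summarises baseline values of the outcome variables descriptively. Section 10.3 states adjustment for the pre-dose value for laboratory markers only.

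**The concern.** An event that happened before treatment cannot respond to treatment. If the window opens at admission and the list includes signs that last for days, a patient who arrives with petechiae, receives study drug and develops nothing further can still be recorded as a bleeding case. The population makes this plausible: all patients enter with very low platelets, which the protocol itself links to bleeding.

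Randomisation balances such cases in expectation, so they do not favour either arm. They add the same amount to both proportions and pull the risk ratio towards 1. A real reduction in new bleeding would be harder to see on a primary objective, and so would a real increase.

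**Working it through.** **Step 1: does the window open before the first dose?** Study Outcome Measures computes length of stay from the date of admission, so in this protocol the stay starts at admission. Admission comes before consent, laboratory confirmation and dosing (Study Enrollment and Withdrawal; Study Schedule). The literal window therefore includes pre-dose time. Its length is not given. Screening covers admitted patients with fever of under 72 hours, while the background says platelets fall over the first 4–6 days of fever, so some patients may spend time in hospital before they reach the entry count. That is an inference, not a stated interval.

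**Step 2: does other text repair it?** Sections 10.2 and 10.3 do not. The first is descriptive and the second covers laboratory markers.

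**Step 3: how large is the dilution?** The protocol's only power statement (80% for a 20% increase in platelet count and hematocrit, section 10.1) does not concern bleeding, so there is no figure of the plan to reproduce here.

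Inputs from the protocol: 50 per arm, 1:1 allocation. Inputs assumed because the protocol gives none:
- the share b with a qualifying sign before dosing, equal in both arms in expectation;
- the proportion p with new or worsened bleeding after the first dose, 40% on placebo and 15% on CPLE;
- a two-sided 5% test.

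The outcome is taken as the proportion of patients with at least one event.

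If pre-dose signs count, the observed proportion is b + (1−b)p, so the difference is (1−b)(p_placebo − p_CPLE). At b = 30%, placebo is 0.30 + 0.70 × 0.40 = 0.58, CPLE is 0.30 + 0.70 × 0.15 = 0.405, and the difference is 0.70 × 0.25 = 0.175. Power is by exact binomial enumeration of the pooled z test. The last column instead leaves out patients with a sign at baseline, so n per arm is 50(1−b).

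| b | Placebo | CPLE | Difference | Risk ratio | Power, pre-dose signs counted | Power, those patients left out |
|---|---|---|---|---|---|---|
| 0% | 40.0% | 15.0% | 25.0 points | 0.38 | 0.82 | 0.82 |
| 10% | 46.0% | 23.5% | 22.5 points | 0.51 | 0.66 | 0.78 |
| 30% | 58.0% | 40.5% | 17.5 points | 0.70 | 0.44 | 0.66 |
| 50% | 70.0% | 57.5% | 12.5 points | 0.82 | 0.25 | 0.53 |
| 70% | 82.0% | 74.5% | 7.5 points | 0.91 | 0.15 | 0.35 |

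Counting new or worsened bleeding in all patients keeps power at 0.82 for any b, provided that patients with a baseline sign have the same 40% and 15% rates of new or worsened bleeding.

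**Step 4: other assumed rates.** At 40% v 20%, power is 0.60 at b = 0, then 0.47, 0.31 and 0.18 at b = 10%, 30% and 50%. At 50% v 25% it is 0.74, then 0.64, 0.44 and 0.27. The direction holds in each case; the size depends on the inputs.

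**The case against.** A reader might infer that the protocol scores pre-dose signs as outcome events and so masks any effect of CPLE. The text does not support that.

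- No section says pre-dose signs will be scored. Incidence of episodes can mean new occurrences. Study Design follows patients for clinical endpoints in hospital until study day 5, so the hospital stay may simply mean in-hospital study follow-up as opposed to the week-2 visit. This stands as an alternative reading. It does not close the gap, because no reference time for new is given, and signs that arise between admission and first dose still fall inside the literal window.
- The difference shrinks by (1−b); it does not disappear. This stands.
- A reader might also infer that the same petechiae will be recorded repeatedly as separate episodes. Twice-daily assessment is a frequency of examination, not a counting rule, so this is conjecture.
- It would be too strong to say that no patient already bleeding is kept out. The background cites guidance under which platelets are transfused below 50,000 with bleeding, and section 5.2 excludes patients transfused before the drug. Some overt bleeders would drop out that way; patients with skin signs only need not.
- Post-dose bleeding can also surface through adverse events, compared by Fisher's exact test in section 10.2. That limits the loss for safety but does not define Primary Objective 3.
- Onset rules often sit in a statistical analysis plan, which section 10.3 promises. The window, however, is stated in this protocol for a primary objective, and a later plan would have to depart from its literal wording.

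**Conclusion.** The point holds as a weakness in how the outcome is defined. The window is not anchored to first dose, the list includes persistent signs, and no new-onset condition is stated, so on a literal reading pre-dose signs can count. If they do, the absolute difference is multiplied by (1−b). In the illustration, even b = 10% takes power from 0.82 to 0.66.

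The event rates and b are all assumed, and balance between arms holds only in expectation. The documents establish the ambiguity and the direction of its effect. They do not establish how many patients would be affected, or that the trial's staff would score bleeding this way. It is a cheap improvement worth making.

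**What to change.** In section 3, reword Primary Objective 3 (3.1) and the primary outcome measures (3.2.1) to the same definition: the proportion of patients with at least one new bleeding manifestation, or worsening of one present at the pre-dose Day 0 examination, from first dose to discharge, or to study Day 5 if discharged earlier. Count a persisting sign once, and use the Day 0 examination as baseline. Anchor the start to the time of the first dose, so that the definition does not depend on whether dosing is labelled Day 0 or day 1. Running the window to discharge keeps bleeding that occurs in hospital after Day 5, which a fixed Day 5 end would lose.

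The cost is wording in two places and a check that the case report form (Appendix I, not shown) records each listed sign before the first dose. The baseline examination and follow-up to Day 5 are already planned, so no visits or patients are added. The downside is that fewer events are counted and staff must judge what counts as worsened, which calls for a short written rule.
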